### **12.3 Allocation to entry number and study treatment**

After inclusion of all subjects, the statistician will randomly allocate the subjects to an entry number and a treatment order, with randomization restricted by plasma homocysteine concentration and smoking.

Entry numbers will consist of the TNO study code (4963), followed by a slash ('/'), followed by a 2-digit number (01-26).

The statistician will inform in writing the Senior Research Nurse and dietician on allocation to entry number and the dietitian on allocation of entry number to study treatment (see also section 8.2.2).

### **12.4 Assessments**

The assessments to be done are summarized in the scheme given in §3.

For logistic reasons, subjects will be divided in two groups, starting their treatment period on two consecutive days. For both series the first day of treatment will be specified as Day 01. All subsequent visits will be divided in these two groups, with visits on two consecutive days.

During the whole treatment period, subjects are not allowed to consume liver, spinach and shrimps; consumption of liver products will be restricted to 2x per week. Also consumption of eggs or egg-containing products will be prohibited or restricted and consumption of products containing lecithin will be restricted. Dietary restrictions start two weeks before day 01 of the study and are described in P4963 B01.

On **Days 01 and 29** subjects will visit TNO at ca. 08:00 h in a fasting state (from 22:00 h the evening before). After filling in a well-being questionnaire, body weight will be measured. Fasting blood samples will be collected and subsequently subjects will ingest a methionine dose (100 mg L-methionine per kg body weight; t=0 h) dissolved in a glass of orange juice (P4963 F08) together with a standard breakfast (P4963 F07) and one portion of study substance mixed with about 200 mL of custard. Blood samples will be collected at 6 h following ingestion of the methionine dose (t=6 h). A lunch without restrictions will be served afterwards. Subjects receive study substances and a diary for the period until the next visit and will be instructed about the storage conditions of the study substances and about how to consume the substances.

On **Days 05 (starting group 1) or 06 (starting group 2) and 35** subjects will visit TNO to fill-in a well-being questionnaire, to check compliance and to collect study substances for the remaining of the treatment period.

On **Days 13 and 41**, subjects will visit TNO between ca. 08:00 and ca. 09:30 h in a fasting state (from 22:00 h the evening before). Subjects have to fill-in a well-being questionnaire. After collection of fasting blood samples, breakfast will be served together with one portion of study substance.

On **Days 15 and 43**, subjects will visit TNO at ca. 08:00 h in a fasting state (from 22:00 h the evening before). Compliance will be checked. After filling in a well-being questionnaire, body weight will be measured. Fasting blood samples will be collected and subsequently subjects will ingest a methionine dose (100 mg L- methionine per kg body weight) dissolved in orange juice (t=0 h) together with a standard breakfast and one portion of study substance mixed with 200 mL of custard. Blood samples will be collected at 6 h following ingestion of the methionine dose (t=6 h). A lunch without restrictions will be served afterwards.

## **12.5 Compliance**

During the treatment periods, subjects will be asked to register the intake of study substances on form P4963 F06b. On this form they will also report deviations from the dietary restrictions. Subjects will have to return unused study substances. The number of study substances returned, registered on form P4963 F03, will be used to check compliance. In addition the empty bowls will be returned and weighed to assess the remaining of the study substances. Compliance to dietary restrictions during the pre-study period and the wash-out period will be checked with form P4963 F06a.

## **12.6 Adverse Events (AEs)**

AEs will be established by the medical investigator on basis of:

1. Answer to the open question: 'How are you feeling?'
2. Spontaneous reporting
3. Well-being questionnaire (Form P4963 F05)

AEs will be classified under the responsibility of the medical investigator according to ICD-10 (published by the WHO) and (P4963 B05). He/she will register his/her findings, conclusions and actions. Increased homocysteine concentrations in plasma following the methionine loading test will not be considered as an adverse event. Additional tests on medical indication can be performed, if required as assessed by the medical investigator.

## **12.7 Serious Adverse Events (SAEs)**

Any serious adverse event, whether or not related to the study treatment will be reported by the medical investigator immediately (within 24 hours) to the principal investigator, the sponsor or its representatives, the TNO Medical Ethics Committee (TNO-METC), the TNO-management, the general practitioner and the study subject. The exception to this rule is that serious adverse events that have already been treated by the general practitioner or medical specialist, or about which the general practitioner or medical specialist have already been informed, which situation is to be judged by the medical investigator, do not have to be reported to the general practitioner or subject. A written report on the event will be sent to the sponsor and the TNO-METC within three working days. See P4963 B05 for a definition of a serious adverse event.

## **12.8 Safety**

The medical investigator will guard the medical safety of the subjects within the frame work of the study. He/she is on call 24 hours per day. During visits with blood collection blood will be collected by an authorized person (authorized by the Medical

Investigator), and a registered nurse or the (assistant) medical investigator will be present in the research facility.

#### **12.9 Post-study screen**

At the last day of the study (or within one week after the clinical part) subjects will have a post-study screen. The post-study screen will involve an interview with the medical investigator.

#### **12.10 Criteria for withdrawal or premature discontinuation**

Subjects may discontinue the trial at any moment without the obligation to state the reason for discontinuation.

Subjects may be withdrawn from the study by the principal investigator if they do not comply with the rules and regulations of the study.

Subjects may be withdrawn from the study by the medical investigator in case of reported serious adverse events or in case of other medical/social/psychological events as evaluated by the medical investigator and discussed with the principal investigator.

Each subject who does not complete the study for any reason should be contacted at least at the end of the particular study day and should have a post-study screen, if requested by the subject or medical investigator.

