The oral methionine loading test as performed in the present study (100 mg/kg body weight) is routinely used in hospitals to diagnose hyperhomocysteinemia. It was also applied in two intervention studies previously carried out at TNO in which healthy subjects daily ingested a placebo treatment or betaine (dosages 1.5g/day to 6 g/day) for 6 weeks. Adverse reactions were reported after (repeated) methionine loading, including faintness, nausea, abdominal complaints, headache, tiredness and blurred vision. Cottington et al. (28) reported the death of a control subject after an oral load of methionine for a study of the possible relationship between homocysteine and Alzheimer's disease. The most likely explanation for this adverse event was a tenfold overdosage of methionine. A number of studies have demonstrated that endothelial function is impaired temporarily following methionine loading (29-31). Recently, the safety and adverse effects of the methionine-loading test were evaluated (32). Acute complications during a standard methionine loading test (100 mg/kg body weight) and the 30 d mortality were assessed in 296 patients with coronary artery or peripheral arterial disease and 591 controls. Acute complications were observed in 33% of the women and 16.5% of the men. Most common symptom was dizziness. None of the subjects died. It was concluded that although standard loading with L-methionine frequently causes transitory complications impairing perception and vigilance, the test does not have serious adverse effects on vasculature and may be considered a safe procedure (32).

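### Section 12.10 gives the closing interview to men who stop early only on request, although 12.9 gives it routinely; a routine offer would close most of a small gap in adverse-event recording

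*Protocol*

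**What the plan says.** Section 12.9 states the general rule: "At the last day of the study (or within one week after the clinical part) subjects will have a post-study screen". It gives the content in one sentence: "The post-study screen will involve an interview with the medical investigator". The schedule in section 3 places this screen at the day 43 visit.

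Section 12.10 states the rule for men who do not complete. Such a man "should be contacted at least at the end of the particular study day", whatever his reason for stopping, and he "should have a post-study screen, if requested by the subject or medical investigator". The same section also provides: "Subjects may discontinue the trial at any moment without the obligation to state the reason for discontinuation".

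Section 12.6 lists three sources of adverse events for the medical investigator: an open question on how the subject feels, spontaneous reports, and the well-being questionnaire (form P4963 F05). Section 11.2.2 ties the questionnaire to visits. On loading days, section 12.4 fixes the order: "After filling in a well-being questionnaire, body weight will be measured. Fasting blood samples will be collected and subsequently subjects will ingest" the methionine, together with breakfast and one portion of study product.

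**The concern.** A man who reaches day 43 is interviewed by the medical investigator without anyone having to ask. A man who leaves earlier is interviewed only if he or the medical investigator asks, and he may leave without giving a reason. Whether the interview takes place can therefore depend on whether somebody already suspects a problem, which makes recording selective.

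Non-serious complaints are to be expected. Section 8.4 says of the institute's own earlier trials: "Adverse reactions were reported after (repeated) methionine loading, including faintness, nausea, abdominal complaints, headache, tiredness and blurred vision". Adverse events are to be presented descriptively (15.3.1), and the report is to include safety data (16). In a study of 26 men, incomplete information on one or two early leavers could show in such a table. What is at stake is how completely non-serious events and their outcomes are described.

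**Working it through.** The plan gives no figure to reproduce. The check compares the two rules and then counts where the questionnaire leaves a gap.

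**The two rules side by side**

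| | At study end (12.9) | Stopping early (12.10) |
|---|---|---|
| Interview with the medical investigator | Routine | On request by the man or the medical investigator |
| Timing | Last day, or within one week | Not stated |
| Contact on the day of stopping | Not applicable | For every non-completer |

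Section 12.9 speaks of subjects without restricting the word to completers. That does not remove the difference, because 12.10 is the specific rule for non-completers and the schedule shows the screen only at day 43.

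**Inputs for the count**

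- Questionnaire visits (section 3): days 01, 05 or 06, 13, 15, 29, 35, 41 and 43, which makes 8.
- Methionine loads (sections 3 and 12.4): days 01, 15, 29 and 43, which makes 4. Each comes after that day's questionnaire.

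**Questionnaires available for a man who stops between a load and his next visit**

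| Stops after the load on | Next questionnaire | Days in between | Completed so far | Completed after that load |
|---|---|---|---|---|
| Day 01 | Day 05 or 06 | 5 − 1 = 4, or 6 − 1 = 5 | 1 of 8 | 0 |
| Day 15 | Day 29 | 29 − 15 = 14 | 4 of 8 (days 01, 05/06, 13, 15) | 0 |
| Day 29 | Day 35 | 35 − 29 = 6 | 5 of 8 (the same four plus day 29) | 0 |

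In the first window the man has completed no questionnaire after any exposure. In the third he has completed none after starting the second product. After the day 43 load no questionnaire follows for anyone, and the interview in 12.9 is the only scheduled contact.

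These counts show where a routine interview would add a record. They do not estimate missed events, which cannot be derived because the protocol states no dropout rate.

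**Extra work under the fix.** Assume that 1 to 4 of the 26 men stop early: 1/26 = 3.8% and 4/26 = 15.4%. That means 1 to 4 additional short interviews.

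**The case against.** The strongest reply is that nothing here is contradictory. Section 12.9 is a general rule and 12.10 a specific one, and together they work as triage: contact everyone, then interview when the man or the doctor wants it. Either can trigger the interview alone. The medical investigator, who establishes adverse events under 12.6, can ask for it on his own judgement.

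Other cover exists as well. Men stay on the ward for about 6–7 h after each load (synopsis, restrictions). A nurse or (assistant) medical investigator is present at visits with blood collection, and the medical investigator is on call around the clock (12.8). The evaluation cited in 8.4 describes the complications of loading as transitory, so many reactions should be seen before the man goes home. Serious events have their own reporting rule (12.7). A completer interviewed on day 43, the day of his last load, has no later scheduled follow-up either.

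All of this stands, and it keeps the point small. It does not remove it. Complaints that arise at home, and the outcome of events still open when a man leaves, fall outside the ward stay. The investigator's discretion helps least when a man leaves without explanation.

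A reader might go further and treat the same-day contact as faulty because 12.10 names no caller, question or form. The protocol does not support this as a separate fault. The open question and spontaneous reporting in 12.6 can be used at that contact, section 12.9 does not list what the completers' interview asks either, and the content of the end-of-trial form in the subject booklet (12.2) is not shown.

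**Conclusion.** The point holds as a minor improvement. The protocol fixes a rule that makes the closing interview routine at study end and request-based for early leavers. In three windows between a load and the next visit, no questionnaire covers the time after that load. A later non-serious complaint, or the outcome of an open event, may then be recorded less completely than in a completer.

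Two stronger readings should be resisted. One is that non-completers have no adverse-event follow-up. They do: the contact on the day is for all of them, and the interview is available on request. The other is that men who leave have probably left for intolerance, so that events are being lost. The protocol gives no reasons for stopping and no dropout rate, so neither the direction nor the number can be stated.

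Efficacy, laboratory and serious adverse event data are unaffected. The conclusion rests on the text of 12.4, 12.6, 12.9 and 12.10 and on the visit schedule. The only assumed figure is the range of 1 to 4 early leavers, which is used solely for the workload.

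**What to change.** In section 12.10, keep the same-day contact and replace the clause "should have a post-study screen, if requested by the subject or medical investigator" with a routine offer, for example:

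> Every non-completer who has taken at least one portion of study product or one methionine load is offered the interview of section 12.9 on the day of stopping or within one week, by telephone if he prefers. The open question of section 12.6 and form P4963 F05 are used. The outcome of open adverse events, and any refusal, is recorded. The blind in section 8.2.2 is kept.

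The cost is one changed sentence and a few short interviews with existing staff and an existing form. A man may still leave without giving a reason, because he can decline the offer. That is also the limit of the change: some men will decline, so the gap becomes smaller and visible but does not close.

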## 13 Code and handling of samples

### 13.1 Sample coding

Blood samples and spot-urine samples collected at the **pre-study** screen will be coded as follows:  
study code (4963), followed by a slash ('/'), followed by the pre-entry number (3 digits), followed by a slash ('/'), followed by the visit-time code (VTC, P4963 B02), followed by (next line) tube code for the type of matrix and volume.

**In study** blood samples collected will be coded as follows: Study code (4963), followed by a slash ('/'), followed by the entry number (2 digits), followed by a slash ('/'), followed by the visit time code (VTC, P4963 B02), followed by (next line) tube code for type of matrix and volume.

For sub-sample tubes, on the second line the tubecode number, type of sample and type of analyses will be indicated. In case more than one sample per type is present, this will be followed by a one-digit number

### 13.2 Sample collection, preparation and storage

#### 13.2.1 Sample collection pre-study

A total of about 22 mL blood will be collected for screening.

For haematology, blood will be collected in Vacutainer® tubes (2 ml) containing K3EDTA as anticoagulant, coded '02-EDTAbI', stored at room temperature and analysed on the day of collection. Non used material will be discarded after analysis.

For serum collection, blood will be collected in Vacutainer® tubes (9.5 ml) containing clot activator and a gel to separate serum and packed cells after centrifugation, coded '05-stolbI'. The samples will be centrifuged 15-30 min after collection, for 15 min at ca.  $2.000 \times g$  at ca. 4°C. After centrifugation serum will be removed and mixed and divided as follows:

- A 2.0 mL aliquot will be used for serum chemistry (05-ser.hit) and stored at  $\leq -18^{\circ}\text{C}$
- A 1.5 mL aliquot will be used for analyses of vitamin B12 and folic acid (05-ser.B/F) and stored at  $\leq -18^{\circ}\text{C}$
- Remaining serum (aliquot of max. 2 mL will be stored as archive serum at  $\leq -70^{\circ}\text{C}$  (05-ser.arc)

For plasma collection, blood will be collected in Vacutainer® tubes (10 ml) containing EDTA, coded 12-EDTAbI. Immediately after collection blood will be mixed well and put on ice. Samples will be centrifuged within 15-30 min after collection for 15 min at ca.  $2.000 \times g$  and ca. 4°C. After centrifugation plasma will be removed and divided as follows:

- A 1.0 mL aliquot will be used for analyses of homocysteine (12-pl.homcy)
- A 1.5 mL aliquot will be used for analyses of vitamin B6 (12-pl.vitB6)

Remaining plasma (aliquots of max. 2 mL) will be stored as archive (12-pl.arc). All plasma samples will be stored at  $\leq -18^{\circ}\text{C}$ .

Spot urine samples, coded '04-uri.spot', will be stored at room temperature and analysed on the day of collection (dipstick) and discarded after analysis. A microscopic inspection of sediment of urine will be done if the dipstick test gives values above the normal range for leucocytes, blood or protein.

Pre-study blood and urine sample collection, subsample presence and transfer will be registered on forms P4963 F09 and P4963 F10 .

#### 13.2.2 *Sample collection in-study*

For serum collection, blood will be collected in Vacutainer® tubes (9.5 ml) containing clot activator and a gel to separate serum and packed cells after centrifugation, coded '05-stolbl'. The samples will be centrifuged 15-30 min after collection, for 15 min at ca.  $2.000 \times g$  at ca.  $4^{\circ}\text{C}$ . After centrifugation serum will be removed and mixed and divided as indicated below. All serum samples, except those meant for analysis of blood lipids and liver enzymes, will be stored at  $\leq -70^{\circ}\text{C}$ . Samples for analysis of blood lipids and liver enzymes will be stored at  $\leq -18^{\circ}\text{C}$ .

For plasma collection, blood will be collected in Vacutainer® tubes (10 ml) containing EDTA, coded 12-EDTAb1. Immediately after collection blood will be mixed well and put on ice. Samples will be centrifuged within 15-30 min after collection for 15 min at ca.  $2.000 \times g$  and ca.  $4^{\circ}\text{C}$ . After centrifugation plasma will be removed and divided as indicated below. Archive plasma samples will be stored at  $\leq -70^{\circ}\text{C}$ , all other plasma samples will be stored at  $\leq -18^{\circ}\text{C}$ .

For heparin plasma collection, blood will be collected in Vacutainer® tubes (5 ml) containing Lithium-heparin as anti-coagulant, coded '03-li.hep.bl'. Immediately after collection, blood will be mixed well and put on ice. Within 30 min after collection samples will be centrifuged for 15 min at ca.  $2.000 \times g$  at ca.  $4^{\circ}\text{C}$ . After centrifugation plasma will be removed and divided over the aliquots indicated below. All samples will be stored at  $\leq -70^{\circ}\text{C}$ .

##### Days 01 and 29 (total about 30 ml blood)

One tube of 10 mL EDTA blood (fasting) will be collected at  $t=0$  and plasma will be divided as follows:

1 mL for homocysteine

1 mL for repeat analysis

0.5 mL for betaine, dimethylglycine and choline; directly to be put on ice until storage

1.0 mL for pm analysis (SAH/SAM); add 0.625 ml 10% perchloric acid and mix

0.5 mL as archive material

One tube of 5 mL lithium heparine blood (fasting) will be collected at  $t=0$  and plasma will be divided as follows

2 x 0.5 mL for pm analysis of methionine and other amino acids

2 x 0.5 mL as archive material

One tube of 10 mL EDTA blood (post methionine) will be collected at  $t=6$  and plasma will be divided as follows:

1 mL for homocysteine

1 mL for repeat analysis

0.5 mL for betaine, dimethylglycine and choline; directly to be put on ice until storage

1 mL for pm analysis (SAH/SAM); add 0.625 ml 10% perchloric acid and mix

0.5 mL as archive material

One tube of 5 mL lithium heparine blood (post methionine) will be collected at t=6 and plasma will be divided as follows:

- 2 x 0.5 mL for pm analysis of methionine and other amino acids
- 2 x 0.5 mL as archive material

Days 15 and 43 (total about 50 mL blood)

Two tubes of 10 mL EDTA blood (fasting) will be collected at t=0 and plasma will be divided as follows:

- 1 mL for homocysteine
- 1 mL for repeat analysis
- 1 mL for vit B6
- 0.5 mL for betaine, dimethylglycine and choline; directly to be put on ice until storage
- 1 mL for pm analysis (SAH/SAM); add 0.625 ml 10% perchloric acid and mix
- 3x 1 mL as archive material

One tube of 9.5 mL clot blood (fasting) will be collected at t=0 and serum will be divided as follows:

- 2 mL for blood lipids and liver enzymes
- 1 mL for vitamin B12 and folic acid
- 1 mL as archive material

One tube of 5 mL lithium heparine blood (fasting) will be collected at t=0 and plasma will be divided as follows:

- 2 x 0.5 mL for pm analysis of methionine and other amino acids
- 2 x 0.5 mL as archive material

One tube of 10 mL EDTA blood (post methionine) will be collected at t=6 and plasma will be divided as follows:

- 1 mL for homocysteine
- 1 mL for repeat analysis
- 0.5 mL for betaine, dimethylglycine and choline; directly to be put on ice until storage
- 1 mL for pm analysis (SAH/SAM); add 0.625 ml 10% perchloric acid and mix
- 0.5 mL as archive material

One tube of 5 mL lithium heparine blood (post methionine) will be collected at t=6 and plasma will be divided as follows:

- 2 x 0.5 mL for pm analysis of methionine and other amino acids
- 2 x 0.5 mL as archive material

Days 13 and 41 (total about 30 mL blood)

Two tubes of 10 mL EDTA blood will be collected (fasting) and plasma will be divided as follows:

- 1 mL for homocysteine
- 1 mL for vit B6
- 1 mL for repeat analysis
- 1 mL for pm analysis
- 2 x 1 mL as archive material

One tube of 9.5 mL clot blood will be collected (fasting) and serum will be divided as follows:

- 2 mL for blood lipids and liver enzymes
- 1 mL for vitamin B12 and folic acid
- 1 mL as archive material

Additional at day 13 (about 5 mL blood)

For pm blood for polymorphisms whole blood will be collected in Vacutainer® tubes (4.5 mL) containing EDTA coded (15-EDTAb1). After collection the tube should be gently rolled horizontally between the hands and divided gently over three tubes of 0.5 mL. DO NOT SHAKE THE TUBE. Tubes should be stored at  $\leq -18^{\circ}\text{C}$ .

During the clinical part about 235 mL blood will be collected. In study blood sample collection, subsample presence and transfer will be registered on forms P4963 F11, P4963 F12, P4963 F14, P4963 F15, P4963 F16, P4963 F17 and P4963 F18.

